### Study outcomes

The main study variable is the improvement on the ventricular function measured angiographicaly as described below. This efficacy outcome is measured as the changes on the LVEF evaluated by a cardiologist blinded to the patients’ clinical follow-up. With this objective, patients undergo cardiac catheterization in two study timepoints: on the date of the intracoronary infusion of either experimental treatment or placebo (visit 3) and at month 6 (visit 5) after infusion.

Secondary efficacy outcomes include clinical evaluation and NYHA functional grade, BNP or N-terminal fragment of pro-brain natriuretic peptide (NT-proBNP) blood levels, echocardiogram, exercise testing according to Naughton protocol, without oxygen consumption as well as biological parameters of the BMMNC product that may predict a good response (cellularity, chemotaxis and stem cell markers: CD133+, CD34+, CD34+/CD177+,CD34+/CD38-, CD34+/CXCR4+, CD34+/DR-, VEGFR2+, CD90+, CD105+, CD73+, CD14-, CD45-).

Study variables regarding safety are measured as appropriate during follow-up visits: adverse events (AEs) and serious adverse events (SAEs), causally related with study interventions or procedures (including marked changes of vital signs, abnormalities physical examinations and out of range laboratory test results). Additionally, the protocol emphasizes the identification of specific adverse events: major cardiac events or MACEs (defined as cardiac death, major arrhythmia, inclusion in heart transplant waiting list, cardiac resynchronization therapy interventions and hospital admission due to clinically relevant adverse cardiac events), symptoms and signs of arrhythmia, evidence of myocardial harm and tumoral biomarkers abnormalities.

The study design, evaluations and assessment timeline for all variables is illustrated in Fig. 1. After product infusion, all patients are followed-up for 24 months according to protocol by interventional or clinical cardiologists at the participating hospitals. Protocol programmed visits are structured in 9 time-points that include two pre-infusion visits (screening and randomization), BMMNC/placebo infusion day, and 6 post-infusion follow-up evaluation time-points according to a decreasing frequency: 24 h, 3 months, 6 months, 12 months, 18 months and 24 months. Trial investigators must ensure that essential clinical, analytical and exploratory data is registered in the study’s Case Report Form (CRF).

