### Manufacturing of BMMNCs/placebo

Following informed consent all patients undergo a bone marrow extraction through repeated aspirations from the posterior iliac crest to a total volume of 100–180 mL using 5 mL syringes (20–30 aspirations) that will be collected in an sterile plastic bag containing ACD-A (1:5 v/v proportion). The entire extraction procedure lapses 20–30 min. BMMNCs are obtained by density gradient centrifugation over Ficoll-Hypaque in an automated cell processor SEPAX (Biosafe). After two washes with a 4% albumin solution, a 50 ml cell suspension will be filtered (50 μm diameter), and aliquots used for cell count, viability tests, microbiological assays and biological determinations (immune phenotype and chemotactic ability tests). From this point onwards, the procedure proceeds as follows: For the experimental group, the cell suspension undergoes a final centrifugation, is re-suspended in 20 ml of lactate Ringer’s solution (containing 1% human albumin and 2.5% glucose) and filtered by a 50 μm filter. The total dose of BMMNCs is within the range of 5-10 × 10^8^ cells. Cell expansion is not used in this protocol. In our previous pilot experience, the minimum percentage of BMMNC recovery after processing was around 20–30% of the total initial cell count, which is enough to obtain a final cellular number in the order of 5–10 × 10^8^ to be infused. Should the number of cells harvested in the final product be insufficient, patient’s data would be excluded from the efficacy analysis. Cell viability is > 95% of BMMNCs, and this concentration is maintained for 24 h at a temperature between 4 °C and 22 °C degrees centigrade, as it has been validated in our laboratory. For the control group, placebo consists of 20 ml of lactate Ringer’s solution (containing 1% human albumin and 2.5% glucose), plus the required volume of red blood cells from the extracted bone marrow, to adjust the hematocrit to 1% for masking purposes. The pre-processed BMMNCs from patients in the control group is re-suspended in a solution containing 4% albumin and 10% dimethylsulfoxide and cryopreserved for future administration via compassionated use (if efficacy data is conclusive after trial interim/final analysis). The autologous BMMNCs or placebo is placed in 2–3 sterile syringes (depending on coronary artery dominance) and is transported to the cardiac units in the participating sites for the infusion procedure.

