### Concomitant medication

All patients must be treated with optimized conventional cardiac insufficiency medication for at least 6 months before the inclusion date and throughout follow-up, involving the use of angiotensin-converting-enzyme inhibitors, angiotensin II receptor blockers, beta-blockers, aldosterone antagonists or other diuretic drugs, potassium supplements etc. Additionally, those patients with ejection fraction lower than 30% may also receive digoxin. Treatment should be optimized following medical judgement according to patient’s symptoms/tolerance (NYHA functional class) and/or BNP levels.

Although the combination of cell therapy with G-CSF has been proven efficacious in previous reports [30], this trial has been designed to evaluate solely the effect of BMMNCs, without any stimulating factors that may interfere with the findings.

However, no other therapy to improve the ventricular function in a mechanical way, as resynchronisation therapy or cardiac transplantation, will be used during follow-up. However, non-responders to a previously implanted defibrillator can be included. In the pilot study performed by our group an inverse correlation was found among basal high-density lipoprotein (HDL) serum levels and LVEF improvement (r = − 0,41, *p* = 0,03) [32]. Consequently, patients with a lower baseline values of HDL could attain a higher improvement in LVEF. On this account, patients included in the study should not be treated with statins affecting HDL blood levels (rosuvastatin, pitavastatin and atorvastatin) 2 months prior to inclusion, as well as throughout follow-up. A wash-out period of two months is established for patients under any prohibited medication prior the inclusion in the study.

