### Data management and statistical analysis

Clinical data is manually registered using a paper Case Report Form (CRF). CRF data is entered in the study database using an Electronic Data Capture (EDC) system. After double data entry, resolution of all inconsistencies, and coding by means of medical dictionaries, a final quality control process will be applied. In case of compliance, the database will be considered error free and will be frozen for the statistical analysis of the data. Sponsor and investigator will have access to the final trial dataset.

A descriptive analysis will be performed including all demographic variables collected, as well as baseline clinical data. Qualitative variables will be summarized using absolute frequencies and percentages, while quantitative variables will be described using the mean, median, standard deviation, maximum, minimum and number of observations.

The efficacy evaluation of quantitative parameters will be performed by comparing basal values (prior to the administration of the product) with those recorded in the follow-up visits, using the paired Student’s t-test (if the variable meets the normality requirements), or the Wilcoxon paired test for all other cases. For qualitative parameters, the Chi-square test will be used.

Two interim analyses will be performed during the study. The first one, to ensure the statistical power of the study, will be performed when the first 20 patients reach a minimum follow-up of 6 months, and will include a new sample size calculation based on these data. In the second one, the main variable under study will be analysed once 6-months of follow-up have been completed in all patients recruited. If the results are positive, patients randomised to the control group will be treated via compassionate-use basis with their own cryopreserved BMMNCs, as early mentioned. Per-protocol analysis (PPA) will be used for all efficacy assessments. All p-values and confidence intervals will be calculated and evaluated using a 95% two-sided confidence level.

Safety analysis is aimed at estimating the number and percentage of patients dropped out due to AEs, the number of patients who have experienced at least one AE, the most frequent AEs and the number of patients who experienced at least one SAE. The 95% confidence intervals will be also determined. Safety evaluation will be performed with intention-to-treat analysis.

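### Efficacy is analysed per protocol throughout, with a low-cell-count exclusion that, as written, acts after randomisation in the BMMNC arm only

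*Protocol article*

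**What the plan says.** In the protocol article, Data management and statistical analysis fixes the efficacy population: "Per-protocol analysis (PPA) will be used for all efficacy assessments". The same section gives the other principle a narrower role: "Safety evaluation will be performed with intention-to-treat analysis".

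Manufacturing of BMMNCs/placebo adds an exclusion: "Should the number of cells harvested in the final product be insufficient, patient’s data would be excluded from the efficacy analysis". The sentence stands among the steps for the experimental group, before the text turns to the control product. That product is described separately: "For the control group, placebo consists of 20 ml of lactate Ringer’s solution" with albumin, glucose and some red cells, so it carries no mononuclear cell dose. Marrow is nevertheless taken in both arms ("Following informed consent all patients undergo a bone marrow extraction"), and the aliquots for counting are drawn before the procedure divides by arm.

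Study population and enrolment says something different. Once a patient has been treated, the only ground for exclusion is withdrawal of consent, and everyone else stays in follow-up, at least for safety.

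Trial design and the analysis section plan an analysis when all patients have reached 6 months. If it is positive, placebo patients may receive their own stored cells.

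**The concern.** Randomisation makes the two groups comparable only if membership of the analysis set does not depend on what happens afterwards in one of them. Here a BMMNC patient with a poor cell harvest leaves the efficacy analysis, while a placebo patient with an equally poor harvest stays in. If harvest is related to how LVEF would change over 6 months, the retained BMMNC patients differ from the placebo group for a reason other than treatment.

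This is a stated choice and not a detail left out of a condensed article. The text names both analysis principles and gives efficacy to one of them. The primary endpoint is affected, and so is the 6-month decision on treating placebo patients.

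**Working it through.** **1. The plan's own figure.** Inputs from Sample size calculation: difference 9 units, common SD 10, correlation 0.5, two-sided alpha 0.05, power 80%, loss 10%, allocation 2:1.

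- SD of change = √(10² + 10² − 2 × 0.5 × 10 × 10) = 10.
- Placebo n = 1.5 × [10 × (1.960 + 0.842) / 9]² = 14.53, rounded up to 15.
- With 10% loss: 15 / 0.9 = 16.7, so 17 placebo, 34 BMMNC and 51 in total.

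The stated 51 is reproduced. The sample size is not at fault.

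**2. Does the exclusion reach one arm or both?** The rule refers to cells in the final product. The BMMNC final product has a cell number; the placebo product has none. The sentence sits in the BMMNC steps, and no matching rule is given for placebo. As written it acts in one arm. It also does not fit the enrolment section, where withdrawal of consent is the only exclusion after treatment.

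**3. What a one-arm exclusion does when the product has no effect.** The documents give neither the share dropped (f) nor the correlation between yield and LVEF change (ρ), so both are assumed. For normal variables the bias is approximately ρ × SD × φ(z_f) / (1 − f), where φ is the normal density and z_f the f-quantile. Example: f = 20%, ρ = 0.5 gives 0.5 × 10 × 0.280 / 0.8 = 1.75.

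A simulation (40,000 runs; 34 v 17; SD of change 10; two-sample t-test of change, two-sided 0.05; the lowest-yield BMMNC patients dropped) gave:

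| Share dropped | ρ | Bias (LVEF units) | False positive favouring BMMNC (nominal 2.5%) |
|---|---|---|---|
| 10% | 0.2 | +0.3 | 3.1% |
| 10% | 0.3 | +0.5 | 3.6% |
| 10% | 0.5 | +0.9 | 5.0% |
| 20% | 0.2 | +0.7 | 4.3% |
| 20% | 0.3 | +1.1 | 5.4% |
| 20% | 0.5 | +1.8 | 8.6% |
| 10% or 20% | 0 | 0 | 2.5% |
| 10% | −0.3 | −0.5 | 1.7% |
| 20% | −0.3 | −1.0 | 1.2% |

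Whole patients are dropped (3 of 34 for 10%, 7 of 34 for 20%), so the simulated bias differs slightly from the formula. Dropping the same fraction in both arms kept the bias within about 0.3 units.

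**4. What keeping low-yield patients costs.** Assume that they gain nothing from the product and that the others gain 9 units. The effect by assigned arm is 9 × (1 − f), and the standard error at 34 v 17 is 10 × √(1/34 + 1/17) = 2.97. Power = Φ(effect / 2.97 − 1.96):

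| Under-dosed share of BMMNC arm | Effect | Power, 34 v 17 | Power, 30 v 15 | Total N for 80% with 10% loss |
|---|---|---|---|---|
| 0% | 9.00 | 85.8% | 81.2% | 51 |
| 5% | 8.55 | 82.1% | 77.1% | 57 |
| 10% | 8.10 | 77.8% | 72.6% | 60 |
| 20% | 7.20 | 67.9% | 62.4% | 78 |

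**The case against.** The best defence is that the rule is set in advance, rests on a product count and not on the outcome, and probably touches few patients: the manufacturing section says that even the lowest recovery in the pilot was enough to reach the intended number. This stands as a limit on the likely size. It does not restore the randomised comparison.

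A second defence is that the wording refers to the patient generally and that cells are counted in everyone before the arms divide, so a rule for both arms may have been meant. That is possible, but it is not what the sentence and its position say.

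Three stronger readings are tempting, and the documents do not support them.

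- *The bias is shown to favour the product.* A reader might infer this because Study outcomes lists cellularity among possible predictors of response. That concerns response to the cells. If the cells do nothing, such a link creates no false positives; the inflation above needs yield to be prognostic in itself, which no section states.
- *Clinical failures are removed as protocol deviators.* The Concomitant medication section says that "no other therapy to improve the ventricular function in a mechanical way, as resynchronisation therapy or cardiac transplantation, will be used during follow-up", and the major cardiac events include "inclusion in heart transplant waiting list, cardiac resynchronization therapy interventions and hospital admission". But the article does not define the per-protocol set or say that such patients leave it. Transplantation itself is not on the event list. Any such removal would act in both arms, and if the product works it could remove more placebo patients and bias against BMMNC.
- *No analysis of all randomised patients exists anywhere.* A statistical analysis plan that is not shown may add one as a sensitivity analysis. The criticism is of the set that the protocol fixes for efficacy.

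**Conclusion.** The point holds as a defect in a stated rule. Efficacy is assigned to a per-protocol set, and one exclusion from that set, as written, applies after randomisation in the BMMNC arm only. The rule also conflicts with the enrolment section. The 6-month decision about placebo patients depends on the resulting comparison.

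The size is conditional. With no true effect, and under the assumed 10-20% dropped and correlation 0.2-0.5, the bias is about +0.3 to +1.8 LVEF units, or 3-20% of the 9-unit target (0.3/9 to 1.8/9). The false-positive risk in favour of BMMNC is about 3.1-8.6% against 2.5%. With no correlation there is no bias, with a negative one the sign reverses, and with few shortfalls the effect is small. Neither the direction nor the amount can be settled from the documents.

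**What to change.** In Data management and statistical analysis, replace the per-protocol sentence with wording such as: *The primary efficacy analysis includes all randomised patients in the arm assigned, whatever the cell number of the product. A per-protocol analysis is a sensitivity analysis.*

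In Manufacturing of BMMNCs/placebo, delete the efficacy exclusion as far as the primary analysis is concerned, and reconcile what remains with Study population and enrolment. If a yield restriction is kept for the sensitivity analysis, apply it to both arms using the count taken before the arms divide. This is approximate, because that count precedes the final centrifugation of the BMMNC product.

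Prespecify how missing angiographic LVEF is handled. Baseline angiography takes place at the infusion visit, after randomisation, so patients who leave before infusion lack both measurements. Deaths before month 6 also need an explicit rule; imputing their LVEF without comment would not be adequate.

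The text change is small but needs an approved amendment. With 27 of 51 patients treated at submission, it should be recorded whether the change precedes any look at results by arm.

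The real cost is dilution. If under-dosed patients gain nothing, power at 34 v 17 is about 82%, 78% or 68% when they make up 5%, 10% or 20% of the BMMNC arm. Restate power on that basis, and use the planned sample-size recalculation to take it into account. Recruitment has been slow (28 enrolled from February 2014 to December 2018), so any increase in sample size is a material burden.

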### Study population and enrolment

The study population is constituted by adult male and female patients diagnosed with idiopathic DC, meeting all eligibility criteria as described in Table 1. A sample size of 51 subjects who are regularly followed-up in the Cardiology Units of the eight participating University Hospitals from the Andalusian Public Health System (Table 2) are included in the study through a competitive recruitment scheme. Before undergoing any trial-related procedures, all patients willing to participate in the study must sign a written informed consent. Study practitioners provide them with information about the study, the investigational product, the purpose, procedures and potential risks and benefits of the study. They are randomly assigned to the experimental or control group following a 2:1 ratio, and are engaged to complete study follow-up visits through an optimised medical attention. Trial subjects can withdraw consent for trial participation at any time. Once the patient has received treatment, withdrawal of consent is the single exclusion criteria considered by the protocol. In all other cases the patient must complete follow-up visits to meet at least safety objectives. In addition, patients who have not received the investigational product infusion can also leave the study when a SAE occurs, or the clinical situation of the patient changes and the investigator considers that an alternative treatment is needed.

**Table 1 Tab1:** Eligibility criteria

INCLUSION CRITERIA	
*Participants meeting all the following criteria will be included:*	
1. Male and female patients between 18 and 70 years old.	
2. Patients who sign the informed consent.	
3. Patient diagnosed with idiopathic dilated cardiomyopathy (using echocardiography).	
4. At least 6 months since dilated cardiomyopathy diagnosis.	
5. Lack of coronary injuries on multi-slice computerized axial tomography scan and/or hemodynamic study performed after the inclusion of the patient in the trial, or prior to recruitment if the patient does not present any angina symptomatology.	
6. Patients under optimised pharmacological treatment for at least 6 months prior inclusion in the trial.	
7. Left ventricular ejection fraction (LVEF) ≤ 40% or LVEF 40–50% if left ventricular end diastolic volume (LVEDV) > 110 ml/m^2^ (measured by echocardiogram).	
8. Presence of sinus rhythm.	

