### Safety and adverse events assessments

In accordance with GCP guidelines, all AEs and SAEs that may occur during the clinical trial (observed by the investigator or reported by the patients) whether or not attributed to the investigational medicinal product, are closely monitored until resolution or stabilization, and registered in the study CRF. Also, investigators report to the sponsor all SAEs within the first 24 h from awareness of the event. AEs will be classified on the basis of the Medical Dictionary for Regulatory Activities (or MedDRA) terminology and summarised for each treatment group and relationship to the intervention. Causality of AEs with the study intervention is assessed by the investigator, and re-evaluated by a person responsible for pharmacovigilance appointed by the sponsor. Furthermore, trial DSMC may review accumulated safety data, when appropriate, and for advising the sponsor concerning the continuation, amendment and termination of the trial.

The clinical trial will be interrupted, if any of the following conditions arise: acute arrhythmia in 3 or more patients randomised to the experimental group, severe toxicity as per WHO scale (> grade 3) related to the infusion of BMMNCs in 3 or more patients, major infections caused by the extraction or infusion procedures in 3 or more patients or mortality related to the infusion of the cell product in 2 or more patients. Trial can also be prematurely ended if the sponsor finds a reasonable cause such as: publication in the scientific literature of unacceptable risks or AEs for patients; or a similar study showing consistent results of no significant health benefits; insufficient commitment by the coordinating or principal investigators; or substantial modifications or suspension of the development of the drug under investigation.

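### Safety is fixed as intention-to-treat although exposure is a single infusion and controls may later receive cells; define the safety set by product received

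*Protocol article*

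**What the plan says.** - **Analysis set.** Data management and statistical analysis (Protocol article) makes all efficacy assessments per-protocol and says of safety: "Safety evaluation will be performed with intention-to-treat analysis". It names no set based on treatment received.
- **Gap between randomisation and infusion.** Trial design puts randomisation at visit 2 and infusion at visit 3. Study population and enrolment adds that "patients who have not received the investigational product infusion can also leave the study when a SAE occurs".
- **Cells for controls.** The second interim analysis takes place once the last patient reaches month 6. If it is positive, "patients randomised to the control group will be treated via compassionate-use basis", using their own cryopreserved cells. Randomisation and blinding process allows controls to be unblinded for this. Trial design describes the eligible controls as *finalized*; the other two sections do not repeat that word.
- **Which events count.** Study outcomes words the safety variables as "adverse events (AEs) and serious adverse events (SAEs), causally related with study interventions or procedures". Safety and adverse events assessments says that all AEs and SAEs, "whether or not attributed to the investigational medicinal product, are closely monitored until resolution or stabilization, and registered in the study CRF", and that AEs are "summarised for each treatment group and relationship to the intervention". The statistical section counts "the number of patients who have experienced at least one AE, the most frequent AEs and the number of patients who experienced at least one" serious event, with no causality limit.

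**The concern.** Confirming the safety of the product and its route is a stated secondary objective, and the placebo arm is there to show what happens without the cells. For a single-infusion product, the natural safety denominator is the patients who started the infusion, grouped by what they received. Counting by assignment departs from this in two ways. Never-infused patients lower the apparent rate of infusion harms. A control who is given cells within follow-up adds cell-related events to the placebo column. The first effect shrinks the absolute risk difference, and the second raises the comparator. Both can make the product look safer than it is.

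The causality wording under Study outcomes is a separate matter. If it governed reporting, the comparison would rest on investigators' attribution rather than on all events by arm. It causes neither of the two effects above.

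**Working it through.** **Denominators.** The plan's own sample size was reproduced first, because the fractions below use it. Inputs (Sample size calculation): difference 9, SD 10, correlation 0.5, two-sided alpha 0.05, power 0.80, ratio 2:1, 10% loss.
- SD of change = 10 × √(2 × (1 − 0.5)) = 10.
- Controls = (1 + 1/2) × (1.960 + 0.842)² × 10²/9² = 14.5, rounded up to 15, with 30 on cells.
- After 10% loss: 15/0.9 = 16.7, so 17; 30/0.9 = 33.3, so 34; total 51.

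This matches the plan.

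**Dilution.** The article gives no number of never-infused patients, so u is an assumption. If u of 34 are never infused, the rate of infusion-related events is multiplied by (34 − u)/34.
- u = 1: 33/34 = 0.97, a 3% relative reduction.
- u = 4: 30/34 = 0.88, a 12% relative reduction. For example, 6/30 = 20.0% reads as 6/34 = 17.6%.

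If the same fraction is never infused in both arms, the rate ratio is unchanged and only the absolute difference shrinks.

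**Window for crossover.** The interim falls when the last patient is at month 6, and follow-up ends at month 24. A control is therefore still in follow-up at the interim if treated less than 24 − 6 = 18 months before the last patient.

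**How many controls could be in that window.** These are scenarios, not forecasts.
- Pace so far: 28 enrolled from February 2014 to December 2018, about 58 months, or 28/58 = 0.48 per month. Over 18 months this gives 8.7 patients, one third of them controls: about 3, and 3/17 = 18%.
- Fast accrual: all 51 − 28 = 23 remaining patients within 18 months gives 23/3, about 8 controls, and 8/17 = 47%.

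These percentages are controls who could be exposed to cells, not events moved. They assume that the interim is positive and that every control in the window is treated.

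**Effect on the placebo rate.** The measures are patients with at least one AE or SAE. A crossed-over control changes such a rate only if the first qualifying event comes after the cells. The ceiling is 1/17 = 5.9 points per patient. Let p be the placebo event rate (assumed 10%), q the added risk after cells (assumed 10% to 30%) and c the number crossing over. The intention-to-treat placebo rate is then p + (c/17)(1 − p)q.
- c = 0: 10%.
- c = 3: 0.10 + (3/17)(0.9)(0.1 to 0.3) = 11.6% to 14.8%.
- c = 8: 0.10 + (8/17)(0.9)(0.1 to 0.3) = 14.2% to 22.7%.

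If only controls who have completed follow-up are treated, c = 0 and there is no effect.

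**The case against.** A reader might infer three stronger things, and the article supports none of them.

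- *That only causally related events are analysed.* One clause under Study outcomes says so, but the statistical section counts every patient with an AE or SAE, and the safety section records all events and summarises them by relationship. This is an inconsistency to reconcile. It does not show that the unbiased comparison has been given up.
- *That events after cells will be booked to placebo.* This needs a positive second interim analysis and treatment within counted follow-up. If *finalized* means that 24-month follow-up is complete, the effect is zero. The statistical section also refers back to what the article has already said on compassionate use, which may carry that limit with it. The article does not say whether events after compassionate treatment enter the trial tables.
- *That each crossed-over control shifts the rate by 5.9 points.* By the interim, every control still in the study has had at least six months of follow-up, a marrow extraction and two scheduled catheterisations. Many may already have an AE, and they would then not move the any-AE rate at all.

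It is also fair to say that keeping all randomised patients is right for harvest harms, since extraction precedes infusion in both arms. Nor does safety oversight rest on this table alone. A monitoring committee may review accumulating data, and the stopping criteria for toxicity, infection and mortality are tied to the infusion or procedures (the arrhythmia criterion is tied to the randomised group).

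Finally, an article may leave detailed censoring rules to a fuller document, so the missing crossover rule is not the finding. The intention-to-treat rule, however, is stated outright. What stands is that this rule fits the exposure poorly, and that the sections on who may receive cells do not agree in scope.

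**Conclusion.** The point holds in limited form. Safety is fixed by assignment where a treatment-received set would answer the question better.

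- Dilution applies to infusion-related events only and is small: 3% to 12% relative for an assumed 1 to 4 never-infused patients among 34.
- Misattribution after crossover is potentially larger but conditional. It is zero if only controls who have finished follow-up receive cells. Otherwise it is at most 5.9 points per crossed-over control, with roughly 3 to 8 controls in the window under the accrual scenarios.

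The event rates, the added risk and the numbers never infused or crossing over are assumptions, because the article gives none. The causality wording is a separate, minor inconsistency. This is a cheap improvement and does not invalidate the planned safety analysis.

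**What to change.** 1. Replace the intention-to-treat rule for safety with: the safety set is all patients who start the infusion, analysed by the product actually received.
2. Cut placebo follow-up at the date of any compassionate BMMNC infusion, and tabulate later events separately under BMMNC exposure. This rule works whichever way the compassionate-use text is read.
3. List events from marrow extraction to infusion for all randomised patients, so that harvest harms and patients who leave before infusion remain visible.
4. Reconcile Trial design, Randomisation and blinding process, and the statistical section on which controls may receive cells and when. Which clinical rule applies is for the sponsor to settle.
5. Under Study outcomes, define the safety variables as all AEs and SAEs, with related events as a subset, in line with the other two sections.

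The cost is a wording change and slightly more tabulation. No new patients, visits or data are needed, because all AEs during the trial are already recorded.
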